## Abstract

**Background:**

With nearly 30 % of the general population experiencing one mental disorder in 12 months, common mental disorders (CMDs) are highly prevalent in Germany and mainly affect the workforce. Therefore, the processes of successfully returning to work (RTW) and achieving a sustainable RTW (SRTW) are important not only for recovery but the prevention of negative consequences like job loss or disability retirement. While factors influencing and predicting the time until RTW are well-investigated in other countries, research on determinants of RTW and SRTW has received little attention in Germany. Consequently, this study aims to investigate the RTW and SRTW processes due to CMDs from the employees´ perspective in Germany.

**Methods:**

This prospective cohort study uses a convergent parallel mixed methods design with a quantitative sample and qualitative sub-sample. Two hundred eighty-six participants of the quantitative study and a sub-sample of 32 participants of the qualitative study were included. The primary outcome of the quantitative study is the time until RTW and full RTW. The secondary outcome is the sustainability of RTW. The following measures will be used to cover work-, RTW- and health-related factors: working time, duration of sickness absences, functional ability, work ability, RTW self-efficacy, social support, work-privacy conflict, job satisfaction, job crafting and depressive symptoms. Quantitative and qualitative data will be integrated at the end.

**Discussion:**

The paper provides an overview on study design, recruitment, sample characteristics and baseline findings of an 18 months mixed methods follow-up study in Germany. This study will provide evidence of (S)RTW processes and its influencing factors due to CMDs in Germany and therefore contribute to further improvement of its (S)RTW practices.

**Trial registration:**

German Clinical Trials Register (ID: DRKS00010903, July 28, 2017, retrospectively registered).

## Background

Mental disorders are widespread in Germany. Twenty-eight percent of the general population between 18 and 79 years experience one mental disorder within a 12 month time period. The highest prevalence rates are observed among younger age groups, mainly affecting the working age (18–34 years: 36%, 35–49 years: 28%, 50–64 years: 26%, 65–79 years: 20%) [1, 2]. The burden, costs and challenges of mental disorders are high for the affected individuals, their employers, companies and society [3–6]. The processes of successfully returning to work (RTW) and achieving a sustainable RTW (SRTW), therefore, play an essential role in recovery and the prevention of further negative consequences like job loss or disability retirement [7–10].

Germany has a mainly community-based comprehensive mental healthcare system without great financial barriers for its use by the patients. Although the prevalence rates of mental disorders are high, utilisation rates of mental health services in Germany are relatively low, e.g. 33% with any 12-month diagnosis of a mood disorder report a mental health service use within the last 12 months, throughout all diagnoses the number is even lower (19%) [11]. Along with it, the German mental healthcare system is fragmented between various service providers (e.g. general practitioners vs. mental health specialists like psychiatrists or medical / psychological psychotherapists), settings (e.g. in- vs. outpatient care) and funding (e.g. statutory health insurances vs. German Pension Insurance scheme) [12, 13]; for a short overview of sectors and service providers see [11]. Despite the huge burden and costs, RTW and SRTW research at the intersection of the mental healthcare system and workplace has received little attention in Germany so far.

Previous research regarding RTW due to common mental disorders (CMDs) in other countries, especially cohort studies in the Scandinavian countries and the Netherlands [14, 15], has been primarily focused on factors influencing and predicting the time until RTW [14–16]. The literature has examined certain individual and external factors that are linked to a shorter time to RTW: Personal facilitators for RTW are higher self-efficacy (RTW-SE), positive RTW expectations, higher work ability and younger age. Disease-related factors are, in particular, the severity of the symptoms and the duration of the sick leave. Work-related factors relate mainly to the social support offered by the line managers and colleagues, as well as the collaboration and communication with employers during sickness absence; other facilitators are a gradual RTW (GRTW), the realisation of job accommodations and the timing of RTW [14–17].

However, much of this research concentrated particularly on the process towards RTW after suffering a mental disorder [18, 19]. According to the conceptualisation of RTW by Young et al. [20], in which RTW is seen as developmental process, two important phases after RTW (‘maintenance’ and ‘advancement’) have often been missing. In addition, as Nielsen et al. [18] pointed out, research that focuses on sustainable RTW (SRTW), investigating work-related measures and resources post-RTW (on individual, group, leadership and organisational levels which help to prevent relapse) is still insufficient, which makes it difficult to give valid recommendations for implementing and supporting SRTW [21]. Another limitation of previous RTW research due to CMDs is its focus on determinants, mostly disregarding research on workplace accommodations and needs for people with mental disorders. A scoping review [22] indicates that such workplace accommodations are not yet fully understood and that future studies should address which workplace accommodations are needed and how they can be realised.

Therefore, the present study was established to provide evidence from Germany regarding determinants of RTW and SRTW within its specific social security system. In addition, work accommodation needs and realised work accommodations during RTW will be considered. Finally, as the RTW and SRTW processes with their interactions are very complex, a mixed methods approach will be used to gain more detailed insights and understandings for the further improvement of RTW and SRTW practices in Germany.

### Aims

The overall aim of this mixed methods follow-up study is to investigate the RTW and SRTW processes at the intersection of the mental healthcare system and the workplace due to CMDs from the employees´ perspective in Germany. The following research aims are addressed in the quantitative study: (1) Identification of determining personal, disease- and work-related factors influencing the time until RTW and SRTW; (2) Description of employees´ RTW and SRTW trajectories and analysis of their relationship with personal, disease- and work-related factors. Research aims of the qualitative study are (1) to illustrate the interaction between personal factors, previous experiences, clinical treatment and work-related factors regarding RTW; (2) Reconstructing and describing the employees´ experiences, behaviours and actions, their implicit knowledge and frameworks for action during RTW. At the end, quantitative and qualitative data analyses will be integrated.

The purpose of this paper is to describe the study design, the recruitment process and the quantitative and qualitative baseline findings with its sample characteristics, particularly taking into account the differences between the treatment settings.

## Methods

### Jurisdictional context

In Germany, employees on sick leave receive full payment from their employer during the first 6 weeks of an illness every year. In small companies with up to 30 employees, employers can get a partial refund for these payments [23]. After 6 weeks of sickness absence, employees receive sickness absence benefits from their (statutory) health insurance (up to 78 weeks per illness every 3 years and about 70% of the full payment [24]). Employees have to hand over a medical certificate from their treating physician to their employer by the third day of absence from work, though a company can demand a medical certificate already on the first day of absence from work. The employer receives no information regarding the employees´ diagnosis and it is not relevant for the payment of sickness absence benefits if the illness was work-related or not.

If a sick leave period lasts longer than 6 weeks, all employers in Germany are legally responsible to offer their employees support to overcome work incapacity, to return to work and to prevent further sickness absences as well as disability retirement. This workplace integration management process has been regulated by law since 2004 and is called *Betriebliches Eingliederungsmanagement* (BEM). Despite the law regulating the setting, i.e. it is an obligation for the employer to offer BEM to the employees, it is not regulated how the process is realised (in each company) and which concrete measures are offered and agreed on by the employee and employer.

One specific strategy to facilitate RTW after long-term sickness absence is ‘gradual return to work’ (GRTW) [25–27]. In Germany, before a GRTW is initiated, physicians, mainly general practitioners (GPs), decide together with the employee which tasks he or she can perform and to what extent. During GRTW, employees are still certified as sick and receive sickness absence benefits, normally provided by their health insurance – or, within 4 weeks after medical rehabilitation, by the German Pension Insurance [28].

### Study design

The present mixed methods follow-up study addresses the processes of RTW and SRTW after sickness absence due to CMDs (depressive disorders, anxiety disorders and adjustment disorders) from the employees´ perspective in Germany. Within this prospective cohort study a convergent parallel mixed methods design is used. The quantitative and qualitative data were collected independently and in parallel. They will be analysed separately and the results will be integrated at the end [29].

### Recruitment and participants

Although the majority of people with mental disorders in Germany is treated in an outpatient setting [30], the study team decided in terms of the outcome of interest, narrow inclusion criteria and feasibility due to the fragmented mental healthcare system to only recruit participants from an inpatient treatment setting. Psychiatric clinics and rehabilitation facilities belong to the main mental health services for the prevention, cure, rehabilitation and continuing care in Germany [31] and were, therefore, further considered. Regarding depression, most acute inpatient services in Germany are provided by psychiatric departments [13]. Hence, psychiatric hospitals with inpatient and day programs were chosen to provide one part of the study group. Medical psychosomatic rehabilitation was chosen to provide the other part of the study group, because it took on greater significance during the last decades in consequence of the enormous increase of disability pensions due to mental disorders in Germany and is also mainly provided as inpatient treatment [32].

To gain access to the target group, the project team cooperated with two psychiatric clinics and three medical psychosomatic rehabilitation facilities. Psychiatric clinics provide help with psychotherapeutic, psychopharmacological and somatic program elements in acute crisis situations as a first responder or via referral through a registered physician by prior appointment. Furthermore, they often provide additional day hospital programs, where patients go home in the evenings and on weekends. The incurred costs are normally paid for by the health insurer.

Whereas acute psychiatric care has its focus on curative treatment, medical rehabilitation facilities provide help `to improve work ability and prevent disability pensions´ (p. 1, Bethge et al. [33]). Hence, medical rehabilitation has its focus on overcoming functional impairments to increase work and everyday life capacity [32]. A stay in a rehabilitation facility can either follow a psychiatric treatment, or, if a psychiatric treatment is not appropriate (e.g. due to less acute or severe symptoms), one can claim benefits for rehabilitation from the German Pension Insurance, where the need for rehabilitation is checked. If rehabilitation treatment is granted, costs are normally taken on by the German Pension Insurance. Psychiatrists and psychotherapists in an ambulant setting or GPs often initiate a rehabilitation treatment when preventive or acute measures were not successful enough. During a stay in a psychosomatic rehabilitation facility, a psychiatrist or medical psychotherapist has the main responsibility for the entire care process [34, 35].

Patients from the cooperating clinics were eligible for the study when they fulfilled the following criteria: (1) aged between 18 and 60 years, (2) sick-listed for less than 6 months during the last 12 months, (3) part-time (at least 15 h per week) or full-time employment, (4) permanent employment or fixed-term employment for at least 18 months, (5) intending to return to work with the former company and (6) treated for a first diagnosis and no more than one further diagnosis of the following list of disorders: a) depressive episode (F32.0, F32.1, F32.2), b) recurrent depressive disorder (F33.0, F33.1, F33.2), c) agoraphobia with panic disorder (F40.01), d) panic disorder (F41.0), e) generalized anxiety disorder (F41.1), f) mixed anxiety and depressive disorder (F41.2), g) adjustment disorders (F43.2). Patients with other disorders not mentioned under ‘Inclusion Criteria’, any current severe somatic comorbidity, minor employment, further qualification, unemployment or early retirement, without any intention to return to work (e.g. to apply for unemployment benefits) or insufficient knowledge of the German language to participate in a telephone interview were excluded.

Cooperating clinicians were briefed on the inclusion criteria and they subsequently recruited potential participants from August 2016 until November 2017. After obtaining approval and informed consent from the interested participants, a short paper-pencil questionnaire regarding the qualifying inclusion criteria, documents including the medical diagnoses and the participants’ date of discharge were delivered to the project team.

### Data collection and measurements

It was planned that 300 participants should take part in four telephone surveys (quantitative study) and a sub-sample of 32 participants should take part in the interviews (qualitative study), see Fig. 1 for the study procedure. Sample size calculation was done by using an unadjusted regression model (log rank test of survival in two groups followed for fixed time, constant hazard ratio; α = .05; 2-sided test; hazard ratio = 0.7; power = 0.80). To ensure adequate statistical power, a total number of *n* = 247 events is required, but it must be assumed that with an adjustment of confounding variables, error variance will be decreasing and therefore power will be further increasing. Moreover, the sample size was deemed appropriate considering a response rate of 85% in comparable study designs, leading to a complete follow-up cohort of 255 participants with four measurements. The sub-sample for the qualitative interviews was selected by 1) additional qualitative approval and informed consent, 2) sex (16 women and 16 men), 3) RTW expectations from the short paper-pencil questionnaire (75% with a positive RTW expectation and 25% with a negative RTW expectation) and 4) first diagnosis from the clinicians (16 participants with depression, six participants with anxiety disorder and six participants with adjustment disorder). The quantitative study team selected the participants for the qualitative sub-sample from the main sample, giving the qualitative study team no information regarding the referred criteria, so that the qualitative study team was as unbiased as possible prior to the narrative interviews.

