#### Characteristics of the participants

Table 2 shows the baseline characteristics for the total cohort as well as stratified by psychiatric and rehabilitation group (due to the afore mentioned differences in the care and funding system). At baseline, participants of the rehabilitation group were on average 3 years older, had more fixed working hours or shift work, less sedentary work, a faster RTW expectation, and reported higher RTW self-efficacy, higher work ability, better self-rated health, greater functional ability and less depressive symptoms than the psychiatric participants. Whereas nearly 36% of the rehabilitation participants were diagnosed with an adjustment disorder as their first diagnosis, all participants of the psychiatric group were diagnosed with a depression or anxiety disorder. The average length of a stay in a psychiatric clinic was more than 2 weeks longer (mean = 7.6 weeks, SD = 1.60) than in a rehabilitation facility (mean = 5.2 weeks, SD = .76; *t* (257) = 16.618, *p* < .001, mean diff. = 2.36, 95% CI [2.08–2.64] η^2^ = .493). Most psychiatric participants received day hospital treatment (76%), whereas almost all rehabilitation participants received inpatient treatment (98%). The median monthly net household income was lower in the rehabilitation group: 2000–3000 Euros vs. 3000–4000 Euros in the psychiatric group (Median Test*, p* < .05). Nearly all participants (97%) had a permanent employment contract.

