Despite the overall response rate, which provides a very good basis for further analyses, some limitations have to be kept in mind. Because the present study was designed as an observational prospective cohort study without a control group, no control over other confounding variables is possible. In Germany, no register data on sickness absence periods are centrally available, so that we had to use self-reported data except for the medical first and second diagnoses from the clinicians. Thereby, the differences in the distribution of the given diagnoses between the two groups could be possibly explained by the different systems and their access paths, care routines, diagnostic procedures and the fact, that patients with adjustment disorders have commonly a shorter duration in the acute psychiatric setting (of the selected cooperation clinics). For this reason, we were not able to recruit study participants with adjustment disorders in the psychiatric setting (as an example see distributions of adjustment disorders of different inpatient units in [61]). As the selection of participants was undertaken with cooperating clinics for reasons of recruitment, the study sample is not representative for patients with a CMD in Germany as well as for the two examined mental health service groups. Furthermore a non-probabilistic sample has been drawn, which should be kept in mind for further analyses. Due to the narrow study inclusion criteria, a healthy entrance effect may have occurred. Finally, as the study was designed from the perspective of the employees, the perspective of the employers and key RTW stakeholders is missing.

To the best of our knowledge, this study is the first of its kind to investigate RTW and SRTW processes due to CMDs in Germany. It addresses an important research gap. One further advantage of this study is the use of well-validated instruments that have previously shown high internal consistency and strong validity. Moreover, the long term observation period of 18 months combined with a mixed method approach will add important knowledge on RTW and SRTW processes over time. As a result, recommendations for employers and other stakeholders on promoting and supporting (S)RTW practices in Germany can be given. Based on that knowledge, interventions can be developed to improve (S)RTW processes and practices in Germany in the future.

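### Adjusting for confounders cannot be assumed to add power in the planned Cox models; for a factor correlated with the covariates, more than 247 events are needed at an adjusted hazard ratio of 0.7

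*Protocol article*

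**What the plan says.** Under Methods, Data collection and measurements, the calculation is described as follows: "Sample size calculation was done by using an unadjusted regression model (log rank test of survival in two groups followed for fixed time, constant hazard" (the quote stops in mid-phrase). The significance level is given as "α = .05; 2-sided test", the effect to be detected as "hazard ratio = 0.7" and the power as 80%, so that "247 events is required". On enrolment, "It was planned that 300 participants should take part in four telephone surveys"; an 85% response rate then leaves 255 people with all four measurements.

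Directly after the event count, the article adds that "it must be assumed that with an adjustment of confounding variables, error variance will be decreasing and therefore power will be further increasing".

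Under Data management and statistical analyses, the factors influencing time to return to work are to be examined with Cox regression, with clinic taken into account as a fixed or random effect. The Discussion describes an observational cohort whose two service groups differ on many baseline characteristics, and asks that this be considered in later analyses.

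**The concern.** The reasoning belongs to linear regression, where a prognostic covariate unrelated to the factor of interest removes residual variance and so sharpens the estimate. A Cox model has no residual error variance to remove. The covariates in question are also called confounders, which means that they are associated with the factor being tested. In that situation adjustment makes the log hazard ratio less precise.

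The sentence works as a safety margin for an unadjusted calculation, and there is little margin elsewhere: 247 events out of 255 expected completers means that 247/255 = 97% of them must return to work. The adjusted models answer the first quantitative aim. A reader who believes that adjustment has added power may take a null adjusted result as evidence that a factor does not matter, when the model had less than 80% power for a hazard ratio of 0.7.

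**Working it through.** **Inputs from the article.** Hazard ratio 0.7, two-sided α = 0.05, power 0.80, 247 events, 255 expected completers, 286 included. The allocation ratio is not stated; 1:1 is assumed because it reproduces the article's figure. R² of the factor of interest on the other covariates is not stated either, so a range is shown.

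**Step 1: reproduce the stated figure.** Schoenfeld's formula at 1:1:

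events = (1.960 + 0.842)² / (0.25 × (ln 0.7)²) = 7.849 / (0.25 × 0.1272) = 246.8, rounded up to 247.

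The article's count is right for the test that it names.

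**Step 2: allow for correlated covariates.** The variance of the adjusted log hazard ratio is inflated by about 1/(1−R²), so

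- events needed = 246.8/(1−R²), rounded up;
- power with D events = Φ(√(D × 0.25 × (1−R²)) × 0.3567 − 1.96).

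Example, R² = 0.10: 246.8/0.90 = 274.2, so 275 events. Power at 247 events: √(247 × 0.25 × 0.90) = 7.455; 7.455 × 0.3567 − 1.96 = 0.699; Φ(0.699) = 0.758.

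| Assumed R² | Events for 80% power | Power, 247 events | Power, 255 events | Power, 286 events |
|---|---|---|---|---|
| 0 | 247 | 80.0% | 81.3% | 85.5% |
| 0.05 | 260 | 78.0% | 79.3% | 83.6% |
| 0.10 | 275 | 75.8% | 77.1% | 81.6% |
| 0.20 | 309 | 70.8% | 72.1% | 77.0% |
| 0.30 | 353 | 65.0% | 66.4% | 71.3% |

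The 255 column supposes that every expected completer returns to work. The 286 column supposes that every included participant is observed to do so.

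**Step 3: what correlations does the article show?** Table 2 gives associations of treatment setting with single baseline factors. With R² = t²/(t² + df) or φ²:

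- depressive symptoms: 2.33²/(2.33² + 280) = 0.02;
- age: 3.25²/(3.25² + 284) = 0.04;
- return-to-work self-efficacy: 4.81²/(4.81² + 278) = 0.08;
- work ability: 5.69²/(5.69² + 284) = 0.10;
- first diagnosis: 0.499² = 0.25, which would mean 246.8/0.751 = 328.6, so 329 events, and 68% power at 247.

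The last is the upper end. It arises because "all participants of the psychiatric group were diagnosed with a depression or anxiety disorder", which leaves an empty cell for adjustment disorders. A joint R² on several covariates would be at least as large as the largest single one among them, but the article does not give it.

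**Step 4: simulation check.** Cox models with 247 participants, all with events, a conditional hazard ratio of 0.7 and one continuous covariate (500 to 600 replicates per scenario):

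| R² | SE unadjusted | SE adjusted | Adjusted power |
|---|---|---|---|
| 0 | 0.129–0.130 | 0.131 | 78–81% |
| 0.10 | 0.129–0.132 | 0.138 | 71–76% |
| 0.25 | 0.128–0.133 | 0.151 | 65–67% |

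The standard error does not fall even when R² = 0, and it rises with R² about as the formula predicts.

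**The case against.** **Adjustment can raise power.** For a strong prognostic covariate uncorrelated with the factor, the same simulation gave 80% power adjusted against 56% unadjusted (covariate log hazard ratio 0.7 per standard deviation). A reader might infer from this point that adjustment always lowers power, and that would be too strong. The gain, however, comes from an unadjusted hazard ratio pulled towards 1, not from lower variance. Adjusted power does not rise above the planned 80% at a hazard ratio of 0.7, and the article speaks of confounders, not of uncorrelated covariates. With real confounding the unadjusted test estimates a different quantity (its rejection rate ran from 5% to nearly 100%), so it is no fair comparator. The comparison here is with the planned 80% at an adjusted hazard ratio of 0.7.

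**The stated 80% is labelled as unadjusted.** This is true, and no power figure is given for the adjusted models. Many of the factors are also scales, to which a two-group hazard ratio does not map directly. What is wrong is the assertion that adjustment takes power further up.

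**Setting against diagnosis is an extreme pair.** A reader might infer that 329 events are required and that 286 participants can therefore never suffice. The article does not support that. It does not name setting as the powered factor. Each clinic belongs to one setting, so with clinic as a fixed effect setting could not be estimated separately. The other single associations worked out above are far weaker.

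**The limitations paragraph.** A reader might see a contradiction with the Discussion's remark that "no control over other confounding variables is possible". It is not one: the sentence concerns other confounders in an observational design without a control group, and it is compatible with adjusting for what was measured.

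**Conclusion.** The sentence is wrong as written for the planned Cox analyses. For a factor correlated with its covariates, a gain in power cannot be assumed, and 247 events give less than 80% power at an adjusted hazard ratio of 0.7. The shortfall is small at R² = 0.05 (about two percentage points) and substantial at R² = 0.30 (about 15 points). An R² of 0.05 is enough to take power below 80% even if all 255 expected completers had an event.

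This rests on 1:1 allocation, an adjusted hazard ratio of 0.7 for a two-level factor, and assumed values of R². The direction of the variance effect does not depend on which R² above zero is taken; the size does. The 247 and the planned 300 were not derived from the sentence, so the sample size calculation itself stands.

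**What to change.** Delete the sentence on adjustment. In its place, state that 247 events and 80% power apply to the unadjusted two-group comparison only, and that an adjusted analysis needs about 247/(1−R²) events for the same power at an adjusted hazard ratio of 0.7. Then either give the range (R² of 0.05 to 0.30: 260 to 353 events, and 78% to 65% power at 247 events) or report, for the main factors, the minimum detectable adjusted hazard ratio at the observed number of events with R² estimated from the data.

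No change to the Discussion's limitations paragraph is needed on this account.

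The cost is rewording and a less favourable power statement. Recruitment ended in November 2017 and follow-up in April 2019, so no design decision is affected. The gain lies in interpretation: null adjusted results should be read with their confidence intervals and not as evidence of no association.
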